## Abstract

Aromatase inhibitors are the standard adjuvant hormone therapy for postmenopausal women with hormone-sensitive breast cancer. However, nearly half of patients experience aromatase inhibitor-associated musculoskeletal syndrome (AIMSS), predominantly pain, which compromises quality of life and treatment adherence. While adapted physical activity offers proven benefits in oncology, its specific role in preventing or managing AIMSS remains unclear. Moreover, the maintenance of physical activity throughout the care pathway in real-world settings is limited, underscoring the need for hybrid approaches that assess both clinical effectiveness and implementation. In response to these challenges, the primary study aim will be to compare the prevalence of musculoskeletal pain at 6 months of aromatase inhibitor therapy between patients who initiate a personalised, adapted physical activity programme at the beginning of the care pathway and those who receive usual care. Secondary aims will be to (1) assess additional effects of the intervention on physical health, psychosocial well-being and treatment adherence, (2) explore contextual factors influencing programme implementation in routine oncology care and (3) identify potential risk factors for the development of AIMSS.

The APIS study is a hybrid type I effectiveness-implementation randomised controlled trial including 182 postmenopausal women with non-metastatic hormone-sensitive breast cancer.APIS will generate new evidence on the clinical and implementation effectiveness of early personalised adapted physical activity in preventing AIMSS. The hybrid design will support the development of sustainable, patient-centred interventions potentially improving quality of life, adherence to hormone therapy and long-term outcomes in breast cancer survivorship.

Trial registration number

NCT07295457.

WHAT IS ALREADY KNOWN ON THIS TOPICAromatase inhibitors are a standard treatment for hormone-sensitive breast cancer and are frequently associated with musculoskeletal pain (AIMSS), which negatively affects quality of life and treatment adherence. Although physical activity is recommended in oncology, evidence for its specific role in preventing AIMSS is limited, and the implementation of exercise interventions in routine care remains suboptimal.WHAT THIS STUDY ADDSTo date, the preventive role of early adapted physical activity on the development of aromatase inhibitor-induced musculoskeletal symptoms has not been specifically investigated.This study combines the evaluation of clinical effectiveness with an embedded implementation analysis using a hybrid type 1 design.It explores the emerging role of advanced practice nurses within an interdisciplinary care pathway to support the integration and sustainability of adapted physical activity in oncology.HOW THIS STUDY MIGHT AFFECT RESEARCH, PRACTICE OR POLICYThis study will provide a more comprehensive understanding of the effects of early adapted physical activity on aromatase inhibitor-induced musculoskeletal symptoms and generate insight into interdisciplinary implementation processes within routine oncology care.

## Background

 Breast cancer is the most frequently diagnosed cancer in women worldwide, responsible for 666 103 deaths in 2022. Approximately 80% of these cases are hormone-sensitive.^1^ In postmenopausal women with non-metastatic hormone-sensitive breast cancer, the standard treatment regimen includes surgery followed by hormone therapy. Depending on tumour characteristics, this approach may be complemented by chemotherapy and/or radiotherapy. Hormone therapy is initiated at the end of primary treatment and continues during the survivorship care period in more than 98.5% of cases.^2^ Aromatase inhibitors (AI) are the standard adjuvant hormone therapy for postmenopausal women with hormone-sensitive breast cancer, effectively reducing recurrence and mortality rates.^1^

AIs can cause AI-associated musculoskeletal syndrome (AIMSS) that affects nearly half of treated women and negatively impacts their quality of life and treatment adherence. AIMSS involves musculoskeletal symptoms such as arthralgia, myalgia and tendinopathy, with pain being the most common and significant symptom.^3^ The physiopathology and predictive factors of AIMSS remain unclear. The physiopathology and predictive factors behind AIMSS remain unclear. They could be linked to oestrogen deprivation, which is known to play a role in maintaining joint and bone health by promoting cartilage regeneration and reducing inflammation.^3^ Both pharmacological and non-pharmacological strategies have been investigated for managing AIMSS, but evidence on accessible and effective therapies for its prevention or treatment remains limited.^4^

Supportive care, particularly regular physical activity (PA), offers many benefits for people with cancer.^5^ Most research focused on women with breast cancer. The practice of PA during and after medical treatment is associated with reduced fatigue,^6^ improved quality of life,^7^ lower recurrence risk and better survival rate.^8^ Schmitz *et al*^9^ emphasise the importance of initiating PA early in the oncology care pathway to prevent the progressive impact of inactivity on physical function. This concern is reinforced by recent evidence showing that skeletal muscle deconditioning can appear within the first weeks of chemotherapy in patients with breast cancer.^10^ Together, these findings have informed the development of international guidelines recommending the integration of PA into oncology care pathways.^5^

To translate these benefits into clinical practice, adapted physical activity (APA) enables trained professionals to support patients in developing individualised PA programmes tailored to their daily lives and care pathways. According to the International Federation of APA, APA is ‘directed toward persons who require adaptation for participation in the context of PA. This involves individualising instruction, matching personal strengths and interests with appropriate activities and adapting environments to promote full participation in PA’.^11^

In this context, the early implementation of APA, initiated at the start of the care pathway, could help prevent or alleviate treatment-related side effects, including musculoskeletal symptoms such as AIMSS. However, to date, no study has specifically investigated the role of PA in preventing AIMSS and current evidence remains insufficient to support exercise-based recommendations for its management.^12^

In real-world settings, many patients with cancer struggle to initiate and maintain regular PA during and after treatment, with adherence to recommended guidelines ranging from only 18% to 41%.^13^ Moreover, fewer than 50% of evidence-based PA interventions in oncology are implemented into routine clinical practice.^14^ This gap highlights the complex, multifactorial barriers to implementation that remain underexplored in exercise oncology. To address this issue, hybrid research designs are increasingly recommended, as they enable the simultaneous evaluation of clinical effectiveness and real-world implementation conditions.^15^

### Study objectives

The primary study aim is to compare the prevalence of musculoskeletal pain after 6 months of AI therapy between patients who started a personalised APA programme at the start of their care pathway and those receiving usual care.

The secondary objective is to explore contextual factors influencing the implementation of the APA programme in real-world oncology care, including perceived barriers and facilitators, based on quantitative and qualitative data collected from both patients and healthcare professionals.

## Method

### Study design

The APIS trial is a type 1 hybrid randomised controlled trial (RCT), evaluating the effectiveness of the intervention, while also collecting data on key implementation factors in real-world conditions.^16^ This study is designed as an open-label, two-arm, parallel, multicentre, RCT. Patients in the experimental group will begin a personalised APA programme at the start of primary treatment (surgery or neoadjuvant chemotherapy), in parallel with their usual treatment, as illustrated in figure 1. Patients in the control group will receive standard care, with the structured APA programme initiated at the beginning of the AI therapy, namely at the end of primary treatment. In the absence of standardised real-world data on when to initiate APA in postmenopausal women with hormone-sensitive breast cancer, the timing chosen for the control group reflects current local practice. Both groups will have no restrictions on autonomous PA during their care pathway.

**Figure 1 F1:**
[figure not shown]
Standard treatment pathway for postmenopausal women with non-metastatic hormone-sensitive breast cancer, including timing of APA programme initiation in the experimental and control groups.AI: Aromatse Inhibitors; APA: Adapted Physical Activity.

In accordance with its secondary objective, the APIS trial also incorporates an embedded implementation evaluation. A concurrent mixed-methods design with methodological triangulation will be used. Quantitative and qualitative data will be collected in parallel, analysed separately and then integrated to explore implementation outcomes.^17^ Patients and healthcare professionals involved in the care of patients with breast cancer will be invited to participate, to capture implementation-related experiences, perceptions and contextual information. The study design is shown in figure 2.

**Figure 2 F2:**
[figure not shown]
APIS study methodology.APA :adapted physical activity; COM-B :Capability, Opportunity, Motivation – Behaviour; RE-AIM : Reach, Effectiveness, Adoption, Implementation and Maintenance; TDF : Theoretical Domains Framework.

The APIS protocol was developed in accordance with the Standard Protocol Items for Randomised Trials (SPIRIT 2025) guidelines for interventional studies, and the intervention is described using the Template for Intervention Description and Replication - Rehab checklist to ensure replicability.

### Study setting

This study will be conducted in two French hospitals: the gynaecological surgery departments of the Saint-Etienne University Hospital and the Lyon University Hospital (Hospices Civils de Lyon).

### Study population

The population will include patients and healthcare professionals.

#### Patients

The inclusion criteria will be: (1) female, (2) aged between 18–75 years, (3) diagnosed with non-metastatic breast cancer, (4) hormone-sensitive breast cancer, (5) indication for treatment with AI, (6) affiliated with a social security scheme, (7) provided signed informed consent.

The exclusion criteria will be: (1) individuals deprived of liberty by a judicial or administrative decision, (2) undergoing psychiatric care for an unstable condition, (3) subject to a legal protection measure (guardianship or curatorship), (4) unable to receive sufficient information due to cognitive disorders or insufficient proficiency in the French language, (5) participating in another interventional study with an ongoing exclusion period at pre-inclusion, (6) presenting absolute contraindications to PA (HAS, 2019, p.61), (7) presenting a locomotor system condition that makes cycling impossible.

#### Healthcare professionals

The inclusion criteria will be: (1) individuals working at the Saint-Etienne University Hospital and the Lyon University Hospital as a surgeon, oncologist, radiotherapist, sports medicine physician, APA instructor, physiotherapist, head nurse, care coordinator nurse or advanced practice nurse, (2) caring for patients treated with AI for non-metastatic breast cancer, (3) having signed the informed consent form.

### Assignment of interventions

Participants will be randomised using Ennov Clinical software. Randomisation will be stratified. The study centre will use a computer-generated pseudo-randomised list prepared in advance by a biostatistician. Given the behavioural nature of the intervention, blinding will not be possible.

### Intervention

The APA programme, delivered by the sports medicine department, will consist of structured exercises supervised by APA professionals and will be identical for all patients enrolled. The only difference between the two groups is the timing of the intervention within the care pathway: either initiated at the diagnosis of cancer or at the introduction of AI. The APA programme will begin, after a medical evaluation, with a 12-week supervised programme. Each week, the patient will have two 1 hour sessions supervised by a physiotherapist and/or an APA instructor. At the end of the initial 12-week APA programme, the sports medicine physician assesses the patient’s progress and goal attainment to decide whether to renew the programme, refer the patient to a supervised community-based PA, or guide her toward self-directed activity.

After 12 weeks, a new medical consultation will be scheduled, and a new renewal or adjustment phase will begin until the end of the trial.

The detailed APA programme is provided in online supplemental file 1.

In addition to this personalised programme, the interdisciplinary care team will encourage patients to remain physically active throughout the rest of the week, according to their individual abilities. The goal will be for patients to develop specific skills that will support long-term lifestyle changes.

### Study design and assessment time

Figure 3 illustrates the study design aligned with the clinical care pathway, including the timing of randomisation, the APA intervention and data collection time points. Data collection will be structured around standardised key events in the treatment pathway: T0 (during the pre-therapeutic phase), T1 (at the initiation of the AI), T_APA_ (at the end of the 12-week personalised APA programme) and T2 (6 months after the initiation of the AI). The assessment times will be defined by the stages of the care pathway, rather than fixed calendar times, to account for variability in treatment protocols. The interval between T0 and T1 may range from 1 month for patients treated with mastectomy alone, to up to 7 months for those treated with surgery, chemotherapy (with or without targeted therapy) and radiotherapy. The interval between T1 and T2 is fixed at 6 months.

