#### Secondary outcomes: risk factors for the development of AIMSS

The APIS study will investigate potential risk factors for the development of AIMSS by examining associations between clinical, demographic, treatment-related and psychosocial variables and the occurrence of musculoskeletal symptoms.

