**Assessments**					
Initial clinical assessments***	**X**				
Clinical assessments†		**X**	**X**	**X**	**X**
Anthropometric measurements‡		**X**	**X**	**X**	**X**
6MWT		**X**	**X**	**X**	**X**
Hand grip test		**X**	**X**	**X**	**X**
Pulmonary function test§§		**X**			
Cardiopulmonary exercise testing¶¶		**X**			**X**
Blood test****		**X**	**X**		**X***
24-hour Holter ECG monitoring††††		**X**			**X**
Self-Report Questionnaires‡‡		**X**	**X**	**X**	**X**
Self-directed physical activity follow-up: email or paper logbook§§		**X**	**X**	**X**	**X**
Data collected/implementation		**X**	**X**	**X**	**X**
Data collected/risk factors for the development of AIMSS			**X**		
Semi-structured interview					**X**
Monitoring of adverse events			**X**	**X**	**X**
Monitoring of APA-related adverse events			**X** EG	**X**	**X**

* Initial clinical assessments performed by the surgeon or APN: clinical examination, identification of barriers and facilitators to regular physical activity during the medical interview and assessment of absolute and temporary contraindications to adapted physical activity.

† Clinical assessments performed by the sports medicine physician.

‡ Anthropometric measurements: weight, height, BMI, waist circumference, four skinfolds.

§ Pulmonary function test: FEV1, PEF, VT, VC, RV, TLC, DLCO correction.

¶ Cardiopulmonary exercise testing: VO₂ peak, VO₂ max, maximal heart rate, VO₂ at ventilatory threshold -VT1-, cardiac output at VT1, heart rate at VT1, blood pressure, oxygen saturation.

** Blood test: lipid profile at V0 and V1 (V2 if abnormal value at V1), fasting insulin and fasting blood glucose at V0 (V1 if abnormal value at V0 and V2 if persistent abnormal value at V1), C-reactive protein at V0 (V1 and V2 if inflammation is suspected).

†† 24-hour Holter ECG monitoring: total spectral power.

‡‡ Self-Report Questionnaires (cf. table 2).

§§ Self-directed physical activity follow-up: type, intensity (Borg scale), duration, frequency of physical activity and adverse effects of PA.

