#### Follow-up visit at the initiation of AI (T1)

At the start of AI therapy, all patients will undergo a clinical evaluation, functional tests, adverse event monitoring and Self-Report Questionnaires. This visit will occur in the sports medicine department and be conducted by a sports medicine physician.

For the control group, the personalised APA programme will start at this stage.

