### Data analysis

#### Quantitative data analysis

The statistical analysis will be performed on the intention-to-treat population.

For the primary objective, the maximum intensity of musculoskeletal pain at 6 months (T2) will be compared between groups using parametric (eg, t-test) or non-parametric (eg, Wilcoxon-Mann-Whitney) tests, depending on data distribution.

Secondary objectives include evaluating the intervention’s effects on outcomes such as physical health, psychosocial well-being and treatment adherence. Analyses will include: (1) between-group comparisons at specific time points (T0, T1, T_APA_, T2), (2) between-group comparisons of change over time (eg, T0–T1, T1–T2) and (3) within-group longitudinal changes across time points.

Univariate and multivariate logistic regression models will explore factors associated with the occurrence of AIMSS. Qualitative variables will be compared using χ^2^ or Fisher’s exact test, as appropriate.

All analyses will be two-sided with a significance threshold of p<0.05. Missing data will be handled using appropriate statistical methods. Analyses will be conducted using R software (R Foundation for Statistical Computing, Vienna, Austria).

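### T_APA falls on AI in every control but before AI in long-pathway experimental women, so general adverse events and pain on AI are sought on a timetable that depends on arm (minor; primary outcome unaffected)

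*Protocol article*

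**What the plan says.** Under Study design and assessment time, the visits after T1 are "T_APA_ (at the end of the 12-week personalised APA programme) and T2 (6 months after the initiation of the AI"). The same section gives the spacing: "The interval between T0 and T1 may range from 1 month for patients treated with mastectomy alone, to up to 7 months" when chemotherapy and radiotherapy are added to surgery, and "The interval between T1 and T2 is fixed at 6 months".

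The start of the programme is what is randomised. Under Study design, "Patients in the experimental group will begin a personalised APA programme at the start of primary treatment (surgery or neoadjuvant chemotherapy"), and Table 1 marks that start at T0. Under the T1 follow-up visit, "For the control group, the personalised APA programme will start at this stage".

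In Table 1 the self-report questionnaires, which include the Nordic-style pain questionnaire, are due at T0, T1, T_APA and T2. The row "Monitoring of adverse events" is marked at T1, T_APA and T2. No other study assessment is scheduled between T1 and T2.

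Two secondary parts draw on what happens over time. Adverse events are monitored throughout. The risk-factor aim means "examining associations between clinical, demographic, treatment-related and psychosocial variables and the occurrence of musculoskeletal symptoms", for which "Univariate and multivariate logistic regression models will explore factors associated with the occurrence of AIMSS". The article does not say at which visit, or over which window, occurrence is counted.

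**The concern.** T0, T1 and T2 are stages of the care pathway and mean the same thing in both arms. T_APA is a stage of the intervention, and the timing of the intervention is the randomised difference. The one assessment that can fall between T1 and T2 therefore sits at different points of AI treatment according to allocation. In the experimental arm it also depends on how long primary treatment lasts, and so on whether chemotherapy and radiotherapy were given.

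The issue here is what is accumulated over a period, not a comparison of values at T_APA. If one group is asked about symptoms on AI at weeks 12 and 26 and another only at week 26, a short-lived or poorly remembered event is more likely to be recorded in the first group. The trial is open-label and these outcomes are self-reported, so unequal solicitation would add to the reporting bias already acknowledged under Limitations.

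**Working it through.** The article states no number of assessments on AI, so there is no figure of its own to reproduce on this point. The count follows from the schedule.

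**Inputs.** Supervised programme: 12 weeks (Intervention). T0–T1: 1 to 7 months. T1–T2: 6 months. Programme start: T0 in the experimental arm (Table 1), T1 in controls. One month is 52.1775/12 = 4.348 weeks.

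**Timing relative to AI start.**

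- Control: T_APA = +12 weeks, always. T2 = 6 × 4.348 = +26.1 weeks.
- Experimental: T_APA = 12 − (T0–T1 in weeks). It is zero at 12/4.348 = 2.76 months.

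| T0–T1 (months) | T0–T1 (weeks) | Experimental T_APA, weeks from AI start | Visits on AI after T1: experimental | Visits on AI after T1: control |
|---|---|---|---|---|
| 1 | 4.3 | +7.7 | 2 | 2 |
| 2 | 8.7 | +3.3 | 2 | 2 |
| 3 | 13.0 | −1.0 | 1 | 2 |
| 4 | 17.4 | −5.4 | 1 | 2 |
| 7 | 30.4 | −18.4 | 1 | 2 |

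If the programme starts some weeks after T0, each experimental value moves later by that lag and the threshold lengthens by the same amount. The pattern is unchanged.

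**Gaps on AI.** Controls: 12 weeks, then 26.1 − 12 = 14.1 weeks. Long-pathway experimental women: 26.1 weeks. Short-pathway experimental women have two visits on AI, but the first comes at about week 8 or earlier instead of week 12.

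**Before AI.** Between T0 and T1 inclusive of T1, controls have one assessment after T0 (T1). Long-pathway experimental women have two (T_APA and T1).

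**Illustration of size, using assumptions not in the article.** Take no true effect and pain at T2 in 40% of both arms (the article's control-arm figure). Let a = proportion with pain at a T_APA visit on AI, q = proportion of these still in pain at T2, and s = share of experimental women with long pathways. Assume T2 does not recover earlier episodes.

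- Recorded at any visit on AI, two visits: a + 0.40 − a·q. One visit: 0.40.
- Difference between arms: s × (a + 0.40 − a·q − 0.40) = s·a·(1 − q).
- Middle case, a = 0.30, q = 0.8, s = 0.5: 0.5 × 0.30 × 0.2 = 0.03, or 3 percentage points.
- Extremes over a = 0.20 to 0.40, q = 0.6 to 1.0, s = 0.25 to 1: from 0 (q = 1) to 1 × 0.40 × 0.4 = 0.16, or 16 percentage points.
- If occurrence is read at T2 only, the difference is 0.

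**The case against.** The strongest reply is that no planned analysis is shown to be biased. Most of its parts stand.

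- **Primary outcome.** A reader might infer that the main result is affected. It is not: T2 is a single assessment at the same time on AI in both arms.
- **AIMSS occurrence.** A reader might infer that AIMSS must look more frequent in controls, or that chemotherapy must look protective. That follows only if occurrence means AIMSS at any visit on AI. The article never says so, its time-specific statements of the pain endpoint point to 6 months on AI, and the window may properly be left to the analysis plan.
- **False-positive rates.** One can compute that a nominal 5% between-arm test of occurrence at any visit rejects about 6% to 27% of the time with no effect (30% prevalence at each visit, correlation 0.4 to 0.8, 60% or 80% long pathways, 82 per arm). Apart from the 82, those inputs are assumed, and the article plans no such test.
- **Adverse events before AI.** A reader might infer over-counting in the experimental arm. An extra visit creates no events, and marking APA-related monitoring at T1 for the experimental group alone reflects a real difference in exposure.
- **Other sources.** Both arms keep a daily logbook that records adverse effects of physical activity, which partly protects APA-related events. Monitoring at T2 may recover earlier events by recall.

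What the reply does not remove is the schedule itself. The logbook, as described, covers adverse effects of physical activity, not general adverse events or AIMSS. The further medical consultations under Intervention are not described as assessments of either. An analysis plan cannot supply an assessment on AI that was never scheduled.

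**Conclusion.** The point holds as a minor one. General adverse events and Nordic-style pain on AI are actively sought twice in every control and once in experimental women whose T0–T1 interval exceeds 12 weeks; before AI the count of visits reverses. This follows from the stated schedule, taking programme start at T0 as in Table 1.

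Any cumulative count of general adverse events or AIMSS over the AI period would then depend on arm and, within the experimental arm, on treatment received. A term for arm alone would not remove the second dependence. How much this matters turns on recall at T2 and on the share of long pathways, neither of which is given; the 0 to 16 point range is an illustration, not an estimate. Only secondary and exploratory analyses are touched.

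**What to change.** - Send the same short adverse-event and Nordic-style questionnaire to both arms at T1 + 12 weeks, through the platform on which patients can already enter data (Quantitative data management). For controls it coincides with T_APA.
- Report adverse events by T0–T1 and T1–T2 windows. Report all of them, but show events elicited only at an arm-specific T_APA separately from the between-arm rates.
- If occurrence of AIMSS in the exploratory logistic models is counted over visits, use only the assessments on AI common to both arms (T1 + 12 weeks and T2), or T2 alone.

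The cost is one extra remote questionnaire for experimental women and a sentence or two in the analysis plan. Choosing T2 alone also drops episodes that resolve before T2 from the risk-factor outcome. Sample size, intervention and primary outcome do not change. The questionnaire should be added prospectively, because information not collected at week 12 can later be recovered only by recall.
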